### Methods in analysis to handle protocol non-adherence and any statistical methods to handle missing data {20c}

In general, participants assigned to the intervention group will be free to avail themselves of the different intervention components or not. The extent to which they do so will be documented, and the relationship of the extent of such use to changes in primary and secondary outcomes will be analysed.

Missing data are only expected in the case of questionnaire data, i.e. for the secondary outcome variables. For the secondary outcome variables that are based on sum scores, missing values will be imputed by the means of those items belonging to the respective variable for which the participant has provided data. A participant who has no baseline value for a specific secondary outcome variable will be excluded from the analyses that refer to that particular variable. However, this participant will be included in all analyses that refer to the variables for which this participant has a value. An intention to treat analysis will be performed for all participants who have a baseline value. In this intention to treat analysis, missing end values will be imputed by taking into consideration the natural development that can be expected for the respective variable for the duration of the intervention. This natural development will be estimated by computing the differences between end and baseline values of the completers in the waiting control group. Accordingly, a missing end value for a particular variable will be estimated by adding the corresponding difference estimated from completers in the waiting control group to the baseline value. Should the resulting value exceed the measurement range of the respective variable, the missing value will be imputed by the range boundary that has been exceeded.

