## Trial design {8}

The trial will be a pragmatic randomised controlled trial with one intervention and one waiting control group. Participants of the control group will receive the P-SUP-programme later than participants of the intervention group. The trial is pragmatic in that it will be performed in the exact setting in which it is ultimately intended to be applied, and in that all resources used will be available if the intervention is ultimately integrated into usual care. The allocation ratio of intervention to control is 6:7 because the drop-out rate for the intervention group is expected to be 30% and, for the control group, 40%. The trial is a superiority study [27] in which the superiority of the intervention to the comparator is to be demonstrated.

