### Sample size {14}

The most important analysis in the evaluation addresses the effect of the intervention on the primary outcome, i.e. the number of hospital days. As mentioned above, intervention and waiting control group will be compared with regard to the change scores of hospital days. These change scores will be computed by subtracting numbers of hospital stays 1 year before intervention start from numbers of hospital stays 1 year before the intervention end. The comparison of change scores will be performed using a *t*-test for independent samples. The sample size has been determined with regard to this test. The basic demand was that the test should be able to detect an effect of size 0.2 with a significance level of 0.05 and a power of 0.8. An effect size of 0.2 is a small effect according to Cohen [39]. However, unpublished analyses of our own with numbers of hospital days indicate that the standard deviation of change scores of hospital days will be between 5 and 10. In this case, an effect size of 0.2 would correspond to differences of one to two hospital days. Even a difference of only one day would mean a substantial difference in costs.

Further conditions presupposed for determining the sample are:
Two percent of the included persons could die during the intervention period or withdraw their consent for their data to be used.There could be a dropout rate of 15% in the intervention group and 20% in the waiting control group. The reason for this assumption is that up to 50% of the sample might consist of persons who are not ensured at AOK RH or BARMER. For these persons, the numbers of hospital days will not be provided directly by the health insurance companies. Instead, the patients will have to request the data from their health insurance companies and then transfer them to the project team. Several patients will not do this, with patients in the waiting control group being more likely not to do this. Within this sub-sample, a dropout rate of 30% in the intervention group and 40% in the waiting control group seems realistic. This would correspond to dropout rates of 15% and 20% in the total sample.The allocation ratio of intervention to control is 6:7.The sample size should be divisible by 13 because of the allocation ratio.

All these considerations imply a sample size of 1001.

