## Data collection and management

### Plans for assessment and collection of outcomes {18a}

The primary outcome, i.e. number of hospital days within the last year prior to the end and the beginning of the intervention, will be sourced from the registers of the collaborating health insurance companies. The information provided in these registers can be assumed to be reliable and valid. The secondary outcomes will be collected using questionnaires sent via postal letter. Most of the secondary outcomes will be assessed using questionnaire modules that are widely accepted in science and for which empirical evidence for their reliability and validity exists. This is the case for self-efficacy with regard to health-related self-management [34, 35], for loneliness [36, 37], for depression [38], for anxiety [38], and for self-reported physical health, which will be determined using the four physical items of the EQ-5D-5L [30]. Self-reported physical activity will be assessed using a modified version of the GLTEQ. The original form of the GLTEQ has been validated [31] and the validity of the modification of the GLTEQ (see Additional File 4) will be investigated in the context of the study. Nutritional behaviour will be assessed using a list of items of behaviour compiled by those responsible for the part of the PSG-leader course that addresses nutrition. The items referring to behavioural intention and perceived behavioural control for both physical activity and nutrition have been formulated according to principles established in social psychology.

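### The missing-data section expects no missing hospital days, but the sample size relies on losing up to 15% and 20% of them by arm, so the primary test as written is a complete-case comparison

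*Protocol article*

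**What the plan says.** The section on non-adherence and missing data {20c} states: "Missing data are only expected in the case of questionnaire data, i.e. for the secondary outcome variables". The rules that follow are set out for the questionnaire variables: item-mean imputation for sum scores, exclusion when a baseline value is absent, and imputation of missing end values from control-group completers.

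Sample size {14} describes a different situation for hospital days. It allows that "up to 50% of the sample might consist of persons who are not ensured at AOK RH or BARMER", and for these people "the patients will have to request the data from their health insurance companies and then transfer them to the project team". It continues: "Several patients will not do this, with patients in the waiting control group being more likely not to do this". The assumed rates are explicit: "Within this sub-sample, a dropout rate of 30% in the intervention group and 40% in the waiting control group seems realistic". For the whole sample this becomes: "There could be a dropout rate of 15% in the intervention group and 20% in the waiting control group".

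Three other places bear on this:
- Section {18b} plans up to three requests to participants of other insurers. It says that collection for AOK RH and BARMER members does not depend on their cooperation.
- Trial design {8} bases the 6:7 allocation on the statement that "the drop-out rate for the intervention group is expected to be 30% and, for the control group, 40" per cent, without limiting these rates to a sub-sample.
- Section {18a} says that the primary outcome "will be sourced from the registers of the collaborating health insurance companies" and does not mention the self-transfer route.

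The primary analysis in {20a} is an independent-samples t-test on the change in hospital days, with no accompanying rule for missing values.

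**The concern.** The section that governs missing data denies a loss that the sample-size section budgets for. An analyst who follows {20c} has no reason to plan for absent hospital days. The t-test would then silently drop everyone who did not send in records.

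That loss arises after randomisation in an unblinded trial. It depends on willingness or ability to cooperate, and the protocol itself predicts that it will be greater in the control arm. If non-senders differ from senders in their change in hospital days, and differ unequally by arm, the primary comparison is no longer protected by randomisation for that part of the sample.

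**Working it through.** **Inputs.** From {14}: N = 1001; allocation 6:7; 2% death or withdrawal of consent for data use; 15% and 20% non-transfer; effect size 0.2; alpha 0.05; power 0.8; SD of change 5 to 10 days. A two-sided test is assumed, because sidedness is not stated.

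**1. Reproducing the sample size.**
- Arms: 1001 × 6/13 = 462 and 1001 × 7/13 = 539.
- Evaluable: 462 × 0.98 × 0.85 = 384.8 and 539 × 0.98 × 0.80 = 422.6, together 807.4.
- Power of the two-sample t-test at 0.2 SD: 0.81.
- The smallest N reaching 0.80 under these losses is 978, or 988 as a multiple of 13. The stated 1001 is one multiple higher and so consistent with these losses.
- With the 2% loss alone, power at 1001 would be 0.877, and about 793 participants would suffice with no loss at all.

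The planned number therefore makes sense only if non-senders are expected to fall out of the primary test.

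**2. How many people this is.** Non-transfer: 462 × 0.98 × 0.15 ≈ 68 intervention and 539 × 0.98 × 0.20 ≈ 106 control, about 174 in total. These are upper planning values. At an other-insurer share of 25% instead of 50%, the rates halve to 7.5% and 10%.

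**3. Would the rules in {20c} cover them?** The end-value imputation needs a baseline value. Under Time points (12.4), the collaborating insurers supply both years retrospectively after the intervention. If participants of other insurers are asked in the same way (an inference), a non-sender has neither year. The rule could not be applied even if it were extended to hospital days.

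**4. Possible bias.** Let g be the mean change among non-senders minus that among senders, in days, within an arm. The observed mean differs from the full-arm mean by −(missing share) × g, so

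bias (intervention − control) = 0.20·g(control) − 0.15·g(intervention).

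With equal g this is 0.05·g. The documents give no value for g, so the rows below are assumptions. The last column is the two-sided rejection rate when there is no true effect. It uses SE = √(1/384.8 + 1/422.6) = 0.0705 SD, z = bias/SE, and rate = 1 − Φ(1.96 − z) + Φ(−1.96 − z).

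| g, intervention / control (SD) | Bias (SD) | Days at SD 5 / SD 10 | Rejection rate |
|---|---|---|---|
| 0.5 / 0.5 | 0.025 | 0.125 / 0.25 | 0.06 |
| 0 / 0.2 | 0.04 | 0.2 / 0.4 | 0.09 |
| −0.2 / 0.2 | 0.07 | 0.35 / 0.7 | 0.17 |
| 0 / 0.5 | 0.10 | 0.5 / 1.0 | 0.29 |

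A positive bias makes the intervention look worse. Reversing the signs of g gives the same sizes in its favour.

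**5. The dropout rates in {8}.** At 30% and 40% the 6:7 ratio equalises the arms: 6 × 0.70 = 7 × 0.60 = 4.2. At the 15% and 20% used in {14} it does not: 6 × 0.85 = 5.1 against 7 × 0.80 = 5.6. The blinding section {17a} expects more primary-outcome data sets in the control group, which fits {14} (423 against 385) and not {8}.

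**The case against.** The 15% and 20% are cautious allowances, worded as possibilities and tied to a maximum other-insurer share. For AOK RH and BARMER members no non-transfer loss arises, and {18b} provides reminders for the others. Equal selection in both arms gives little bias. A separate analysis plan may exist and may handle missing hospital days. All of this stands, and it limits what can be said about harm. It does not remove the contradiction: {20c} makes a positive statement that {14} refutes, so the point is not mere silence left to another document.

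A reader might infer more than the documents support:
- **A bias as large as the one-day target difference.** At SD 5 this needs non-senders to differ by 5 days, a full SD, in the control arm only (0.20 × 5 = 1.0). No document supports that value. With non-senders having more days, it would also make the intervention look worse, not better.
- **A trial with only 71% power.** That follows from applying the rates in {8} to whole arms (about 317 each), which {14} and {17a} contradict.
- **Exclusion of participants who die.** Section {14} pools death with consent withdrawal in one 2% allowance and does not say how deaths are analysed.
- **A claim in {18a} that the registers are the only source.** It does not say so, and {18b} describes the second route directly afterwards.

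**Conclusion.** The contradiction is established from the protocol's own text and figures. The trial is sized for up to 15% and 20% loss of its primary outcome (about 385 against 423 evaluable, power 0.81), while the missing-data section says that no such loss is expected. As written, the primary test is a complete-case comparison with loss that depends on cooperation and is predicted to differ by arm. The term complete-case is an inference from the sample-size arithmetic, the bare t-test and the placing of the imputation rules under the secondary outcomes.

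The harm is possible but not quantified. It is small if selection is equal in both arms. It could reach a meaningful fraction of the 0.2 SD target if selection differs by arm, in either direction. The figures assume a two-sided test and an other-insurer share of 50%, and they shrink in proportion to that share.

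**What to change.** 1. **Section {20c}:** state that hospital days are expected to be missing for some participants of other insurers, at up to 15% (intervention) and 20% (control) of the arms.
2. **Primary analysis:** prespecify how missing hospital days are handled for all randomised participants. Multiple imputation by arm, using baseline survey variables and the randomisation strata, is one reasonable choice. Add a delta-adjusted sensitivity analysis in which the shift may differ by arm.
3. **Supporting analysis:** repeat the comparison in AOK RH and BARMER members only, whose data do not depend on cooperation. At a 50% share this is about 226 against 264 people with power near 0.60, so it should be read for consistency of the estimate and not as a second test.
4. **Section {8}:** reconcile the 30% and 40% given there for the groups, and the allocation rationale built on them, with {14}, which limits those rates to the sub-sample.
5. **Section {18a}:** name the self-transfer route already described in {14} and {18b}.

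The cost is protocol or analysis-plan wording and some extra analysis, with no new data collection. One limit remains: if non-senders have no hospital days in either year, imputation rests on survey items and strata alone, which is why items 2 and 3 are both needed.

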#### 12.4 Time points

Hospital days will be sourced from the register data of the health insurance companies. These data are updated continuously. The collaborating health insurance companies will provide these data for evaluation after the intervention retrospectively to the point in time 1 year prior to the start of the intervention. The change scores for hospital days will be computed by subtracting the number of hospital days in the year directly before intervention start from the number of hospital days in the year directly before the end of the regular intervention, i.e. directly before month 18 after intervention start. Data for the secondary outcomes will be collected via a questionnaire (1) at enrolment (baseline survey), (2) 9 months after the start of the intervention (midterm survey), (3) 18 months after the start of the intervention (end survey) and (4) 27 months after the start of the intervention (follow-up survey). The baseline survey will be performed before the study participants have been informed about their assignment to one of the two study conditions. For the questionnaire variables, the core evaluation of the intervention will be based on the change scores between the values of the baseline survey and the values of the end survey, i.e. the survey at month 18 after intervention start.

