## Statistical methods

### Statistical methods for primary and secondary outcomes {20a}

To test the effect of the intervention on the primary outcome (i.e. on number of hospital days), the number of hospital days directly before the start of the intervention and the number of hospital days directly before the end of the intervention will be determined. The differences between these numbers will be computed, and the intervention and control groups will be compared with regard to these differences using a *t*-test for independent samples.

As outlined above (see the ‘Objectives {7}’ section), the effect of the intervention on the number of hospital days is assumed to be mediated by several different variables. Each step of the mediation will take some time. For this reason, there may well be no effect on the primary outcome although effects on the preceding variables are already identifiable. Such a pattern of results would also indicate an effect of the intervention. Consequently, if there is no statistically significant effect for the primary outcome, the pattern for the secondary outcomes will be applied in order to decide the effectiveness of the intervention. For this purpose, all secondary variables will be z-transformed and poled so that higher numbers mean better outcomes in all variables. All variables transformed in this way will be subjected to a two-factorial analysis of variance with the variables as a within-subjects factor and the study condition as a between-subjects factor. The intervention will be judged as effective if there is a statistically significant effect in favour of the intervention group. To judge whether the secondary outcomes actually determine the primary outcome, the relationships between secondary outcomes and primary outcome will be analysed using a cross-lagged panel approach with data from baseline and end surveys as predictors and the number of hospital days for the corresponding time intervals as criteria.

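### Each missing month-18 questionnaire value is filled once with the control completers' mean change and then analysed by an ordinary ANOVA, so intervals are too narrow and the estimate may be biased towards no effect

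*Protocol article*

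**What the plan says.** Section {20c} of the protocol article defines an intention-to-treat analysis of the secondary outcomes for everyone with a baseline value. In it, "a missing end value for a particular variable will be estimated by adding the corresponding difference estimated from completers in the waiting control group" to that person's baseline. The rule applies to both arms. A result outside the scale is set to the scale limit. Partly missing sum scores are first completed from the person's own remaining items. Someone without a baseline value on one variable is left out for that variable, but "this participant will be included in all analyses that refer to the variables for which this participant has a value".

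Section {20a} then specifies a "two-factorial analysis of variance with the variables as a within-subjects factor and the study condition as a between-subjects factor" on z-transformed variables. If the primary outcome is not significant, this analysis decides whether the intervention is judged effective.

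Section 12.2 makes change from baseline the analysis metric. Section 12.4 bases the core evaluation on baseline and month 18, although a further questionnaire is sent "9 months after the start of the intervention (midterm survey"). The article describes no multiple imputation, variance correction or alternative missing-data assumption for these outcomes.

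**The concern.** Because the metric is change from baseline, own baseline plus a fixed difference means that, apart from truncation at the scale limits, every non-responder in either arm gets the same change score: the control completers' mean. The article does not say outright that these values count as observed data, but that is what a single fill followed by a plain ANOVA amounts to.

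Two things follow. The sample size is counted in full while the filled records add almost no spread, so the standard error falls as more data are lost. And the intervention arm's mean is pulled towards the control mean in proportion to its missing fraction.

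At stake is the reported size and precision of the secondary effects and, when the primary test is not significant, the verdict on the programme.

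**Working it through.** **The plan's own figure.** Section {14} requires that "the test should be able to detect an effect of size 0.2 with a significance level of 0.05 and a power of 0.8", and states "The allocation ratio of intervention to control is 6:7". Sidedness is not stated; two-sided is assumed here. Control n = (1 + 7/6) × (1.96 + 0.8416)² / 0.2² = 425.2, so 426, with 365 in the intervention arm. Retention is 0.98 × 0.85 = 0.833 (intervention) and 0.98 × 0.80 = 0.784 (control). The minimum total is (13/6/0.833 + 13/7/0.784) × 196.2 ≈ 975, or 988 as a multiple of 13. At 1001 power is 0.81. The stated 1001 is reproduced closely enough, and gives 462 and 539 randomised.

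**Inputs for this check.**
- Arm sizes nI = 462 and nC = 539.
- The only SD of change given is for hospital days ("the standard deviation of change scores of hospital days will be between 5 and 10"), so the work is in SD units with SD = 1.
- True effect d = 0.20 (assumption, borrowed from the primary design).
- Questionnaire missing fractions mI and mC are not stated. The pairs 15%/20% and 30%/40% are taken, as an assumption, from the dropout rates in sections {14} and {8}. Section {14} derives them for hospital-day records.
- Values missing completely at random; truncation not modelled.

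**Formulas.**
- Expected estimate after filling: (1 − mI) × d
- Reported SE² = (1 − mI)/nI + (1 − mC)/nC
- Actual sampling variance of that estimator = (1 − mI)/nI + (1 − mI)²/[nC(1 − mC)], because the control completers' mean also fills the intervention arm
- SE² that the observed data support (completers) = 1/[nI(1 − mI)] + 1/[nC(1 − mC)]
- Two-sided type I error = 2 × [1 − Φ(1.96 × reported SE / actual sampling SD)]

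**Example, 15%/20%.** Reported: √(0.85/462 + 0.80/539) = 0.0577. Actual: √(0.85/462 + 0.7225/431.2) = 0.0593. Completers: √(1/392.7 + 1/431.2) = 0.0698. Ratios: 0.97 and 0.83.

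| Missing I/C | Estimate of 0.20 | Reported SE | Actual SD | Completer SE | Reported/actual | Reported/completer | Type I error | Coverage of 0.20 by 95% CI |
|---|---|---|---|---|---|---|---|---|
| 10%/10% | 0.18 | 0.0601 | 0.0601 | 0.0668 | 1.00 | 0.90 | 5.0% | 93.7% |
| 15%/15% | 0.17 | 0.0585 | 0.0585 | 0.0688 | 1.00 | 0.85 | 5.0% | 91.9% |
| 15%/20% | 0.17 | 0.0577 | 0.0593 | 0.0698 | 0.97 | 0.83 | 5.7% | 91.1% |
| 20%/15% | 0.16 | 0.0575 | 0.0559 | 0.0699 | 1.03 | 0.82 | 4.4% | 90.0% |
| 30%/30% | 0.14 | 0.0530 | 0.0530 | 0.0758 | 1.00 | 0.70 | 5.0% | 79.5% |
| 30%/40% | 0.14 | 0.0513 | 0.0550 | 0.0786 | 0.93 | 0.65 | 6.8% | 76.7% |

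The coverage column assumes that non-responders benefited like completers, so it combines bias and narrow intervals.

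**Simulation of the composite.** Eleven variables, assumed correlation 0.3, 4,000 runs per scenario. Under no effect the filled analysis rejected in 5.5% (15%/20%) and 7.3% (30%/40%) of runs, against 4.9% (15%/15%) and 4.6% (30%/30%). With a true 0.20, coverage was 85% at 15%/20% and 51% at 30%/40%; complete-case analysis gave about 95% in both.

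**Re-standardisation.** Section {20a} does not say whether z-scores are formed before or after filling. If after, the SD also shrinks: √[(392.7 + 431.2)/1001] = 0.907 at 15%/20% and √[(323.4 + 323.4)/1001] = 0.804 at 30%/40%. The 0.17 and 0.14 become about 0.19 and 0.17.

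**The case against.** **The test is not generally broken.** A reader might infer that every p-value from this rule is wrong. The figures do not support that. Effect and standard error shrink together, so with equal missingness type I error stays at 5% and power matches that of completers (0.83 for both at 15%/15%). With more loss in the intervention arm the test is slightly conservative. Section {20a} also requires significance in favour of the intervention, and the error in that direction is half the two-sided figure: about 2.8% at 15%/20% and 3.4% at 30%/40%, against 2.5%. This objection stands.

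**The shrinkage may be intended.** Participants may stop activities at will, and section {20c} justifies the fill by the course expected without the programme. If intervention non-responders really follow the control course, the smaller estimate is a conservative choice and not a bias. This also stands. It does not supply a variance that allows for the imputation.

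**The missingness rates are borrowed.** In section {14} they concern patients who fail to obtain hospital-day records from their insurer, not postal questionnaires, for which reminders are planned. They show only that the investigators expected less cooperation from the control arm there.

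**Two further readings go too far.** The control arm's own standard error is understated by its missing fraction, but that is not the error in the treatment comparison, where the shortfall against the estimator's actual sampling SD is 3% to 7%. Nor does the article show that the within-subjects ANOVA would discard many participants: partly missing sum scores and missing end values are filled, so essentially only a missing baseline variable removes someone, and allocation is disclosed only after the baseline questionnaire is returned. Leaving out month 9 is an openly stated choice that costs information; it is not a contradiction.

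**Conclusion.** The concern holds in this form: a single deterministic fill followed by an ordinary ANOVA reports more precision than the observed data support, and it attenuates the effect by the intervention arm's missing fraction. The attenuation is a bias only if non-responders there benefited like completers.

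Over the assumed range of 15%/20% to 30%/40%, the reported standard error is 0.83 to 0.65 of what the observed data support, and 0.97 to 0.93 of the shrunken estimator's own sampling SD. The harm is mainly in the estimates and intervals. The excess of false positives is modest and depends on the control arm losing more questionnaires.

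The direction follows from the rule itself. The size rests on assumed missingness, missing completely at random, no truncation and standardisation before filling. A separate analysis plan may add sensitivity analyses, but the rule criticised is the one this article fixes. It deserves correction because it feeds an analysis that can decide effectiveness.

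**What to change.** Replace the single fill with a likelihood-based mixed model for repeated measures using all available baseline, month-9 and month-18 values, and report the arm difference in change at month 18. For the composite, use a corresponding mixed model over all available z-scores, so that one missing scale does not remove a participant. State how and when the z-scores are formed. If the control-based assumption is wanted, implement it as reference-based multiple imputation with proper variance and present it as a sensitivity analysis.

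The month-9 data are already being collected, so the cost is wording, standard software and a little more analysis work. The downside is somewhat wider intervals.
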